**Table 1 Tab1:** **Inclusion and exclusion criteria**

Inclusion criteria	Exclusion criteria
• 65 years or older	• Medical conditions such as the presence of: unstable angina, uncontrolled congestive heart failure, unstable arrhythmia, COPD stage III or IV which contraindicate following a program of physical activity
• Resident in Barcelona, community-dwelling	
• Assigned to one of the 8 PHCC	
• Can attend on-site the consultation room at the PHCC	
• Will stay in the reference area a minimum of one year and a half	• Home Care Program or institutionalization at baseline. Planned admission to nursing home
• Frailty inclusion criteria:	• Participation in other physical activity program
• score of 1 point or above in the Barber Questionnaire	• Has been operated on hip and/or knee the last 6 month (walking independently with technical assistance is not a contraindication)
• Fried modified frailty criteria: 3 or more	
• Gait time between 10 to 30 seconds in the Timed Get Up and Go test	• Suffering a non-controlled neoplastic disease, terminal or severe disabling illness
• MEC-35 of Lobo ≥18 points (no severe cognitive impairment)	• Cannot understand Spanish
• Capable of consent. Agreement to participate in the study

**Figure 1 Fig1:**
[figure not shown]
**Study flow diagram.**

Eligible patients who agreed to participate in the study were invited to sign the informed consent. Baseline variable collection was carried out by the CMN. Patients were then randomly assigned to the intervention and control groups. The computer-assisted simple randomization process was performed not by the recruiters but by an independent researcher. Random allocation sequence was implemented using sequentially numbered containers. Sequence was concealed until the interventions were assigned. Baseline and outcome measurements were blinded to group assignment. Follow-up evaluations are conducted by blind trained clinical researchers.

### Measures

Both cohorts receive identical baseline and follow-up evaluations. Table 2 shows the different time points when variables are measured.

**Table 2 Tab2:** **Measurements at several time points**

	Selection	Baseline		After intervention		18 months	
	All	IG	CG	IG	CG	IG	CG
**FRAILTY MEASURES**							
Barber Questionnaire	x						
Fried modified criteria	x					x	x
SPPB		x	x	x	x	x	x
FRT		x	x	x	x	x	x
Unipodal Station		x	x	x	x	x	x
Strength of upper extremities		x	x	x	x	x	x
Strength of lower extremities		x	x	x	x	x	x
**FUNCTIONAL ASSESSMENT**							
Lawton & Brody Scale		x	x			x	x
Barthel Index		x	x			x	x
**NUTRITION**							
MNA		x	x			x	x
**COGNITIVE EVALUATION**							
MEC-35 of Lobo	x						
Short and Medium-Term Verbal Memory		x	x	x	x	x	x
Animal Naming Test		x	x	x	x	x	x
Evocation of words		x	x	x	x	x	x
Designation of famous people names		x	x	x	x	x	x
Verbal designation of images		x	x	x	x	x	x
Verbal abstraction of word pairs		x	x	x	x	x	x
**DRUGS and PRESCRIPTION**							
Total number of drugs		x	x	x	x	x	x
Psychotropic Medication presence		x	x	x	x	x	x
Withdrawal of drugs				x	x	x	x
**OTHER VARIABLES**							
Comorbidities		x	x			x	x
Biological measurements		x	x			x	x
Analytical parameters		x	x			x	x
Sphincter incontinence		x	x			x	x
Visual impairment		x	x			x	x
Auditive impairment		x	x			x	x
Technical support aids		x	x			x	x
Quality of Life: SF12		x	x			x	x
**ADVERSE OUTCOMES**							
Falls		x	x			x	x
Fractures		x	x			x	x
Hospital admissions		x	x			x	x
Home care inclusions						x	x
Institutionalizations						x	x
Death						x	x

Fried modified criteria for frailty [3] (three or more of the following criteria have to be present): Unintentional weight loss (3 kg in past 6 months)Self-reported exhaustion (2 questions from CES-D scale)Weakness (5 chair stand-up test, unable)Slow walking speed (more than 10 seconds) evaluated by Timed -up-and-Go test (TGUGT). This is a reliable test for quantifying functional mobility (lower extremities function) and for measuring balance (fall risk). The person may wear their usual footwear and can use any assistive device normally employed. The TGUGT is conducted using a chair with arms, and a seat height of 46 cm, placed upon a flat surface with a line marking the 3m turning point. Subjects are instructed on the word ‘go’, to get up and walk as quickly and as safely as possible to cross the line marked on the path, turn around, walk back to the chair and sit down again. The activity will be timed from the subject’s back leaving the back of the chair to the return of the subject to this same position.Low physical activity measured by the IPAQ Questionnaire[53].Physical performance: 2.1*Short Physical Performance Battery*.The short physical performance battery (SPPB) is a simple standardised objective assessment tool of lower limb function[16] that tests standing balance, ability to repeatedly stand from a sitting position, and habitual gait speed. Each component is scored between 0–4 (total score 0–12) with higher scores indicating better functioning. In community-dwelling older adults, lower SPPB scores predict greater risk of mortality, nursing home admission, hospitalization, and incidence of disability. The SPPB consists of:2.1.1)*Balance test*Participants are asked to hold three increasingly challenging standing positions for 10 seconds each: (1) a side-by-side position, (2) semi-tandem position (the heel of one foot beside the big toe of the other foot), (3) tandem position (the heel of one foot in front of and touching the toes of the other foot).2.1.2)*Repeated chair stands test*This is performed using a straight-backed chair, placed with its back against a wall. Participants are first asked to stand from a sitting position without using their arms. If they are able to perform the task, they are then asked to stand up and sit down five times, as quickly as possible, with arms folded across their chest. The time to complete five stands is recorded and used for future analyses.2.1.3)*Gait speed* (*8 meters walk*)2.1.3)2.2*Functional Reach Test* (FRT).This is a valuable test used to measure standing balance and stretching, detecting balance impairment over time. It can predict the risk of falling. After the examiner explains and shows the FRT, each subject performs 2 trial tests. Functional reach is measured by using a levelled yardstick attached to the wall at the height of the subject’s right acromion. To measure the subject’s reaching distance, an examiner stands 0,5 m away from the measuring tape and records the end reach position, checking that the initial position is correct: subjects stand comfortably with feet approximately shoulder-width apart, just before a line marked on the floor at the same level as the measuring tape beginning (0cm); participants then extend the right arm parallel to the yardstick and, without touching the wall, place the third metacarpal along the measuring tape and have to reach as far forward as they can without losing their balance (end position). Subjects are allowed to balance on their toes; however, touching the wall, stepping while reaching forward, or holding onto their clothing with the left hand invalidate the trial. If invalidated, the trial is repeated with a maximum of 2 tests more to achieve 2 valid trials. All subjects are protected during the test. The best result from the two attempts is recorded.2.3*Unipodal station*The patient is placed in a standing position, arms crossed over the chest, with one leg used for support in an extended position, and the other slightly bent at the knee (there can be no contact between the two legs). Once placed in the correct position (eyes open), the chronometer is activated and then stopped when either the patient moves the foot used as a base or when 30 seconds have passed; two attempts with the same foot are made and the best result recorded.Muscle strength. 3.1*Evaluation of upper extremities strength* is assessed through the measurement of force with a handgrip dynamometer. *Grip strength* is assessed using a portable hand dynamometer (JAMAR®0-90 kg, coding 506320). The participants are seated with their shoulder in a neutral position and their elbow flexed at 90°. Three attempts are performed alternately in each hand; the mean of the three measures is recorded.3.2*Evaluation of lower extremities strength* is assessed through the bilateral measurement of the quadriceps muscle force using a digital dynamometer (Chronojump 1.4.5-1.4.6 Boscosystem® Encoder).Activities of Daily Living (ADL) assessment: 4.1* Lawton & Brody Instrumental Activities of Daily Living scale*[54].This is an instrument assessing independent living skills which are considered more complex than the basic activities of daily living. The instrument is most useful for identifying how a person is functioning at the present and for observing improvement or deterioration over time. There are 8 domains of function measured with the Lawton & Brody scale. Women have been traditionally assessed in all 8 areas of function whilst men have not been asked about the domains of food preparation, housekeeping, and laundering. Individuals are scored according to their highest level of functioning in that category. A summary score ranges from 0 (low function, dependent) to 8 (high function, independent).4.2*Barthel Index of Basic Activities of Daily Living*[55].First developed in 1965, it measures functional disability by quantifying patient performance in 10 activities of daily life. These activities can be grouped according to self-care (feeding, grooming, bathing, dressing, bowel and bladder care, and toilet use) and mobility (ambulation, transfers, and stair climbing). 5-point increments are used in scoring, with a maximal score of 100 indicating that a patient is fully independent in physical functioning, and a lowest score of 0 representing a totally dependent bed-ridden state.Nutritional Assessment:*Mini Nutritional Assessment* MNA®[56]. The MNA consists of four parts: anthropometric measurements, general status, diet information, and subjective assessment. A score of less than 17 points (out of a maximum of 30) is regarded as an indication of malnutrition, 17–23.5 points indicate a risk of malnutrition and >23.5 points indicate that the person is well nourished.Neuropsychologist Performance:The first neuro-psychometric instrument developed in Spain to measure semi-quantitatively cognitive status in clinical neurology was the Barcelona Test (BT). A shortened version of the BT, named Barcelona Test Review[57], is used for neuropsychological area evaluation in our participants and it takes only 20–30 minutes to administer. Tests applied are: 6.1.*Short and Medium*-*Term Verbal Memory* is the capacity to hold a small amount of information in the mind in an active, readily available state for a short period of time (seconds) and medium-term period of time (minutes). For the condition referred to as short term, subjects will be instructed to listen to a little story text, 21-pieced-sentences (elements), read by a blind evaluator; once finished, the patient will be asked to repeat the general content and as many details as he or she can remember; the duration of short-term memory is believed to be in the order of seconds. Then, the participant will be submitted to other cognitive trials to divert attention. After 25 minutes, the subject is directly asked for the story again to evaluate medium-term verbal memory. A commonly cited capacity of short and medium-term is 7±2 elements.6.2.* Animal Naming Test* consists of asking the patient to name as many animals as possible in one minute. A blind evaluator must write down the answers, so they can be checked for duplicate responses (repeated words invalidate one of them). The goal of this test is to score at least 14.6.3.* Evocation of words* beginning with one explicit letter, similar to the previous test, in this case the participant will tell the examiner as many words beginning with “p” as possible in three minutes (repeated words invalidate one of them). All kinds of words are allowed, except plurals or the masculine and feminine of the same word, conjugating verbs, and diminutives. The goal of this test is to score at least 27.6.4.*   Designation of famous people names*, the identification of 30 famous faces and their corresponding name permits an examination of the semantic brain area and can identify a possible clinical syndrome of prosopagnosia. Evaluated by “success”, “failure” or “tip of the tongue (TOT) phenomenon”, goal is 23 success, 3 failure, 4 TOT.6.5.*   Verbal designation of images*. Fourteen pictures of different objects or animals are presented to participants and they have to identify each name as quickly as they can: if subjects guess the name between 0–3 seconds this signifies 3 points, between 3–10 seconds, 2 points, and if takes 10–30 seconds it represents 1 point. If the patient does not recognize the picture-name, it is equivalent to 0 points. Goal of the test is to score 41 points.6.6.*  Verbal abstraction of word pairs*, also called “Similarities – Abstraction”, explores patients’ concept formation ability, as the participant must “extract” the common abstract element that links the two words featured. Through this test the ability to discriminate “concrete thinking “from” abstract thought” can be evaluated. The goal of this test is to score at least 5 of 6 pair of words.Medication 7.1.Number of prescribed drugs.7.2.Number of prescribed benzodiazepines.7.3.Presence of antidepressants (yes/no).7.4.Withdrawal of drugs (yes/no).7.5.Number of drugs retired at the closing date of the study.Quality of life. 12-Item Short-Form Health Survey (SF-12) [58].Adverse Outcomes: Falls, fractures, hospital admissions, institutionalization, inclusion in a Home-Care Program, or death.

### Independent variables

Age. Gender. Marital status. Cohabitation. Education Level. Socioeconomic status. Existence of elevator in the building. Provision of regular company.

Co-morbidities assessed in the clinical record: osteoarthritis, fractures in the last 5 years (hip fracture specified), presence of prosthetic joints, vision impairment, hearing impairment, cardiovascular diseases (hypertension, stroke, ischemic heart disease, arrhythmia, congestive heart failure, intermittent claudication, chronic venous insufficiency), pulmonary diseases (Chronic Obstructive Pulmonary Disease (COPD), asthma), endocrinology diseases (diabetes, dyslipidemia, obesity, hypothyroidism, hyperthyroidsim), hematological (anemia), neurologic (Parkinson’s disease), psychiatric (anxiety, depression), chronic kidney disease.Comorbidity measured with Charlson Index [59].Biological variables: weight, height, body mass index, waist circumference, blood pressure.Analytical variables: hemoglobin, serum lipid profile, serum protein, serum albumin, glomerular filtration rate, plasma creatinine, glycated hemoglobin, ferritin, iron, vitamin D, vitamin B12, folic acid.Incontinence (urinary, fecal, both).Urinary catheter (yes/no).Wearing a diaper (yes/no).Usual sensation of light-headedness.Smoking (non-smoker, ex-smoker, current smoker).Devices for mobility (cane, walker).Falls, fractures, and hospitalizations in the previous year.

#### Intervention

The intervention consists of a triple disability preventive therapy, consecutively applied to each subject in the intervention group, in groups of 16 participants (see Table 3):

**Table 3 Tab3:** **Description of Interventions**

3.1 Description of the rehabilitation therapy			
Basic exercise	Alternative exercise		Muscle group
▪ Chest Press against elastic resistance - sitting on a chair	▪ Chest Press against the wall		▪ Pectoral muscles
▪ Reverse Butterfly against elastic resistance - sitting on a chair			▪ Upper back muscles
▪ Arm press against elastic resistance - sitting on a chair	▪ Arm press against elastic resistance - standing position		▪ Muscles of the arms, and shoulders
▪ Stand up with palms on thighs - sitting on a chair	▪ Stand up using hand weighs - sitting on a chair		▪ Quadricep, hamstring, and gluteal muscles
▪ Lift the legs with hands on hips - sitting on a chair			▪ Hip flexor muscles
▪ Hip abduction/adduction - sitting on a chair	▪ Hip abduction/adduction - standing position		▪ Abductor/Adductor muscles
▪ Knee flexion - sitting on a chair	▪ Knee flexion - standing position		▪ Hamstring muscles
▪ Knee extension - sitting on a chair			▪Quadricep muscles
▪ Heel raises - sitting on a chair	▪ Heel raises - standing position		▪ Gastrocnemius and soleus muscles
**3.2 Description of the memory workshops**			
**Memory**	**Language**	**Sensory activation**	**Reasoning and calculation**
Short and Long-Term Visual Memory	Evocation of words beginning with different letters	Series of logical visual pattern recognition	Gnosia and praxia different developing techniques (reproduction of pragmatic models)
Short and Long-Term Written Memory	Crosswords	Marking edge of silhouettes	Letters and numbers matching through Maze Paths
Short and Long-Term Oral Memory	Completeness of unfinished sentences	Coloring components of Hidden Figures Test	Executive functions enhancing: abstract concepts of similar but different objects
Short and Long-Term Musical Memory	Oral communication with clue words	Spot the differences between two pictures	Identification of the inappropriate word in a pool of words
Working memory: identification of hidden figures test	Word search	Picture copies execution	Reading and exclusion of senseless sentences
Memorize an image and draw it from memory	Synonyms and antonyms	Objects, materials and sounds recognition with closed eyes	Filling the gap
True/False sentences	Matching words and their meaning	Group interaction by singing and musical performances	Numerical skills practice: operations and mental agility
Logos recognition	Visual-verb generation task: denomination of images, objects, parts of the human body	Famous faces recognition	
Geographical memory practice	Rearrange letters to form a word and rearrange words to form grammatical sentences		
**3.3 Description of the polymedication review**			
**Who does the intervention?**	**What are the objectives and criteria?**		**How is the intervention performed?**
2 doctors from the Project Group.	To reduce drug prescription of polymedicated patients* if possible, following :		A personalized e-mail is sent to each GP responsible for the patient participating in the intervention group throughout the first week of patient inclusion.
	-Stopp criteria,		
	Depending on the baseline drug prescription at the beginning of the study.		Every e-mail considers the individual profile of the patient referred and tries to adapt the general criteria to each particular case.
			The GP who regularly attends the intervention patient performs both reduction and re-education of unnecessary drugs. This approach should be done in a maximum of 3 clinical interviews specifically designed for this subject.
			E-mail content suggests the most recommended changes but the final decision corresponds to the discretion of the physician responsible for the patient.

*Polymedicated Patient: one that takes more than five drugs daily and continuously for a period not less than six months.

Rehabilitation therapy plus the posterior intake of 1 hyperproteic nutritional shake which is then taken daily for 1 month. All patients in the intervention group perform the aerobics exercise plan in the primary care centre, 60-minute session twice a week on non-consecutive days for 6 weeks (12 sessions of 60 minutes each). Subjects must incorporate a progressive increase in the intensity of the exercise in each session. One session a week is dedicated to work with balance and the other to strength training. Both balance and strength are based on functional exercises. All sessions begin with a warm up for 5 minutes, and end by cooling off for another 5 minutes with relaxing exercises. The sessions are conducted under the supervision of a specialist in physical activity. A hyperproteic nutritional shake is provided at the end of each session, and the amount of shakes needed for one month’s consumption post-physical therapy is assigned. The safety of the exercise program is measured by reviewing the record sheet for each patient in the training program, ascertaining cardiovascular decompensation and musculoskeletal injuries.Memory workshops. Two speech therapists from the rehabilitation unit conduct 12 sessions of practical exercises (written, oral, corporal, and musical) in groups of 16 participants. Each of the 12 sessions lasts 90 minutes and is conducted twice a week. Each person in the intervention group has their own material to work short and long-term memory, with exercises for the identification of figures and images, evocation of words, true or false sentences, crosswords, completion of unfinished sentences, and other language exercises such as synonyms and antonyms.Medication Review. Reduction of potentially inappropriate medications, especially in polymedicated patients, after review from general practitioners. A patient is considered to be polymedicated when taking more than five medications daily and continuously for a period not less than six months. Medication review follows the Screening Tool of Older Persons’ potentially inappropriate Prescriptions (STOPP) criteria [60]. In addition to the review of medication, verbal guidance on each of the drugs consumed is also provided. After an e-mail sent with the changes suggested by two doctors from the Project Group, this intervention is carried out by every patient’s general practitioner, during the first month of the intervention, in a maximum of 3 clinical interviews for that purpose. It especially focuses on reducing the consumption of benzodiazepines or other psychotropic drugs.

The intervention group also receives two group sessions regarding dietary advice, lifestyles, and home hazards.

#### Control group

Subjects in the control group continue with their daily activities and receive regular monitoring and treatment of their diseases by their general practitioners. They are also invited to two group sessions regarding dietary advice, lifestyles, and home hazards.

### Statistics

Intention to treat analyses will be performed. Baseline characteristics will be compared between groups by independent t tests and Chi-square tests. Outcome variables will be calculated for each individual and time point (difference between the result of SPPB, muscle strength, and other frailty variables in each time point and the initial value), and 95% confidence intervals for the differences between groups will be calculated. Data will be analysed using repeated measures analysis of variance (ANOVA) consisting of intervention and control groups and time (baseline, post-intervention, follow-up).

Also, for longitudinal adverse outcome measures (disability, home care inclusion, institutionalization or death), survival analyses using Cox’s regression models will be applied. The statistical significance level will be set at p <0.05.

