### Sample size calculation

Sample size has been calculated to detect minimal significant effects on the variable of physical performance (SPPB): Accepting an alpha risk of 0.05 and a beta risk of 0.20 in a bilateral contrast, 318 individuals are required in order to detect a difference equal to or greater than 0.5 units in the SPPB[49, 50]. The common standard deviation has been taken to be 1.42. A drop-out rate of 20% is anticipated. Finally, 352 subjects have been included (n = 176 IG and n = 176 CG).

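### Change scores and a repeated measures ANOVA with baseline as a time level give up the precision of baseline adjustment, and the ANOVA's standard terms are not the contrast used for sizing

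*Protocol article*

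**What the plan says.** The Statistics section defines each continuous outcome as a change: the "difference between the result of SPPB, muscle strength, and other frailty variables in each time point and the initial value". It plans 95% confidence intervals for the differences between arms in these changes. It then plans a repeated measures ANOVA made up of the two "groups and time (baseline, post-intervention, follow-up"), so baseline is one of three outcome levels. No baseline covariate is named, and the section does not say which ANOVA term or contrast is the test. The Abstract adds a multivariate analysis of time changes without naming covariates.

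The Study design section places the main comparison of changes from baseline at month 3. It uses month 18 to see whether effects last.

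The Sample size calculation rests on one two-group difference: "318 individuals are required in order to detect a difference equal to or greater than 0.5 units in the SPPB". The other inputs are a two-sided test at the 5% level, 80% power, an SD of 1.42 and an expected loss of one fifth of participants. The section does not say whether 0.5 and 1.42 refer to the score or to its change. In the end 352 people were included, 176 per arm.

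**The concern.** In a randomised trial the baseline value is the cheapest source of precision for a continuous outcome. Subtracting it fixes its coefficient at 1. Fitting it lets the data set the coefficient, which is below 1 whenever baseline and follow-up have similar spread and correlate imperfectly. The change score therefore over-corrects. Allocation here is by simple randomisation, so nothing in the design balances baseline SPPB, and chance imbalance feeds directly into the change-score estimate.

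The ANOVA raises a second question. The sample size concerns one difference at one time. The usual ANOVA outputs are a group effect averaged over visits, one of which precedes randomisation, and an omnibus interaction. Neither is that single difference. If one of them were taken as the main result, it would not by itself show at which visit the arms differ, or by how much.

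**Working it through.** **1. The plan's own figure.** Inputs from the Sample size calculation: difference 0.5, SD 1.42, two-sided alpha 0.05, power 0.80, loss 20%.

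n per arm = 2 × (1.96 + 0.8416)² × 1.42² / 0.5² = 126.6, so 127. Total 254, and 254 / 0.80 = 317.5, so 318. The figure reproduces, and 318 already includes the drop-out. With 352 included, completers are 176 × 0.80 = 140.8, about 141 per arm.

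**2. Change score against baseline adjustment.** Let s be the score SD, equal at both visits, and rho the baseline to follow-up correlation. Rho is not in the article and is assumed.
- Residual variance of the change score: 2(1 − rho)s²
- Residual variance after adjustment (ANCOVA): (1 − rho²)s²
- Ratio, ANCOVA over change: (1 + rho)/2, below 1 for every rho below 1

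Power = Φ(0.5 / (SD × √(2/141)) − 1.96), with s = 1.42:

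| rho | SD, change | SD, ANCOVA | Variance ratio | Power, change | Power, ANCOVA |
|---|---|---|---|---|---|
| 0.3 | 1.680 | 1.355 | 0.65 | 70.5% | 87.3% |
| 0.5 | 1.420 | 1.230 | 0.75 | 84.0% | 92.7% |
| 0.7 | 1.100 | 1.014 | 0.85 | 96.8% | 98.5% |

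If 1.42 is instead the SD of the change, change-score power is 84.0% at any rho, and ANCOVA power is 95.6%, 92.7% and 89.4% at rho 0.3, 0.5 and 0.7. The two readings agree only at rho 0.5 and must not be mixed.

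**3. The same loss seen through chance imbalance.** The SE of the baseline difference is 1.42 × √(2/176) = 0.151, so differences up to 1.96 × 0.151 = 0.30 are ordinary. Given an imbalance D, the change-score estimate is shifted by −(1 − rho)D. At rho 0.5 and D = 0.30 this is 0.15 in size. Over repeated randomisations it averages to zero; it is part of the variance in step 2, not an extra bias.

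**4. The ANOVA terms** (compound symmetry, 141 per arm, score SD 1.42, rho 0.5).
- *Group main effect.* A difference of 0.5 at both follow-ups becomes (0 + 0.5 + 0.5)/3 = 0.33; a difference at month 3 only becomes 0.17. The SD of the three-visit mean is 1.42 × √((1 + 2 × 0.5)/3) = 1.159, and the SE is 1.159 × √(2/141) = 0.138. Power for the sustained effect is Φ(0.333/0.138 − 1.96), about 67.5%.
- *Group-by-time.* This is a 2-df F test with noncentrality (141/2) × Σ(d − mean d)² / (s²(1 − rho)). For differences 0, 0.5, 0.5 the sum of squares is 0.1667, the noncentrality 11.65 and power 87%. For 0, 0.5, 0.25 the sum is 0.125, the noncentrality 8.74 and power about 75%.

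**The case against.** The strongest reply is that the plan already contains the right estimate. The Study design section compares month-3 changes between arms, and the Statistics section gives confidence intervals for between-arm differences in change at each time point. Under randomisation the difference in mean month-3 change has the same expectation as the difference in month-3 score. It is therefore unbiased for the 0.5-unit contrast, and it shows both the visit and the size. This stands. A reader might infer that the planned analyses miss the sized contrast altogether; that is true only of the ANOVA terms.

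Second, the 67.5% for the group main effect belongs to a term the article never names as its test. Group-by-time is the more natural term for a comparison of changes, and for a sustained effect it has 87% power at rho 0.5. This also stands, so 67.5% is not the power of the trial. It shows only why that term should not carry the conclusion.

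Third, "Baseline variable collection was carried out by the CMN" (case management nurses), whereas clinical researchers do the follow-up assessments. A reader might infer that change scores carry an assessor bias. The documents do not support this: measurements are blinded in both arms, so a systematic shift is common to both and cancels. Random assessor noise only lowers rho, which the range above already covers.

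Fourth, covariate detail may sit in an analysis plan that is not shown. That would answer a missing detail, but here the article fixes an unadjusted method in writing.

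**Conclusion.** The point holds as a loss of efficiency, together with an ANOVA whose standard terms are not the sized contrast. It is not a bias.

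At 141 completers per arm, with 1.42 as the score SD, the gain from adjustment is 16.8 power points at rho 0.3, 8.7 at 0.5 and 1.7 at 0.7. With 1.42 as the SD of change it is 11.6, 8.7 and 5.4 points. These figures rest on an assumed rho, equal SDs at baseline and follow-up, and 20% loss from 352. The direction does not depend on which rho below 1 is chosen.

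A reader might infer that the trial is underpowered. The documents do not support that. On the score reading, change-score power at 141 per arm is below the planned 80% at rho 0.3 but 84.0% at 0.5; on the change reading it is 84.0% throughout.

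**What to change.** Make the main analysis the month-3 difference between arms in SPPB, adjusted for baseline SPPB, with its 95% CI. Treat each other continuous outcome measured at month 3 in the same way, adjusting for its own baseline value. Give month 18 as a separate adjusted contrast. Table 2 schedules the Lawton & Brody scale, Barthel Index, MNA and SF-12 only at baseline and 18 months, so for these the month-18 contrast is the only one.

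ANCOVA at each visit is enough. A repeated-measures model of the two follow-up visits with baseline as covariate, or a three-visit model with baseline means constrained equal between arms, does the same job. Do not base conclusions on the ANOVA group main effect or the omnibus interaction. State whether 0.5 and 1.42 refer to the score or to the change.

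The cost is a small change of model. The baseline values are already collected in both arms, so no new data are needed.
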